### Data analysis

Data will be entered into SPSS for Windows (version 23). Descriptive statistics such as frequency, percentage, and mean will be used to summarise the outcomes and other variables. The main analysis will be a comparison between both intervention groups and the control group for the proportions of smoking abstinence at 3 and 6 months, using chi-square tests and odds ratios with 95% confidence intervals. Generalized Estimating Equation (GEE) models will be applied to test the intervention effect, to identify the baseline predictors of successful quitting and to assess the changes in smoking-related factors over time. Intention-to-treat (ITT) analysis will be used in which participants who lose contact or drop out in the follow-ups will be treated as a failure to achieve any cessation outcome. Multiple imputations will be used to compute missing data for outcome variables.

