## Abstract

**Background:**

Actively referring smokers to smoking cessation (SC) services could increase quitting and is scalable for the population. The objective of this study is to compare 2 different intensities of SC active referral for smokers in the community of Hong Kong.

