Comparing with traditional telephone cessation assistance, interventions delivered via text messaging are more convenient and accessible, which could potentially extend the reach to SC services [4] and promote SC [13–15]. A recent meta-analysis of 15,593 smokers (20 RCTs) showed that the overall odds of smoking abstinence in text messaging group were 1.37 times higher than the control group [16]. The intensity of interventions in previous RCTs varies, in terms of the frequency, intensity and duration of text messaging in the intervention period, the degree and methods for personalization and tailoring of the text messaging. Substantial evidence has shown that intensive interventions produce more abstinence than less intensive interventions in the clinical setting [4]. Therefore, it is assumed that active referral intervention delivered via high-intensity text messaging will also result in more abstinence when compared with low-intensity text messaging. This study aims to evaluate the effectiveness of 2 different intensities of active referral interventions: (1) high-intensity active referral to SC services and (2) low-intensity SC service referral by using text messaging. The control group will receive general brief SC advice.

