## Discussion

To the best of our knowledge, this is the first RCT conducted to evaluate whether high-intensity active referral to SC services is more effective than low intensity of SC referral by using text messaging in achieving abstinence among smokers in the community. Since the efficiency of active referral of SC services (moderate level of SC active referral by collecting smokers’ details and send to SC providers for follow-up) has been proved in the previous trial [11], the present study explores further by comparing the efficacy of the 2 different intensities of SC active referral. We also expect that active referral with high intensity will achieve high rates on smoking abstinence and smoking reduction by comparing the effectiveness of HAR, moderate level SC active referral and text-messaging referral in a 2-year combined model.

This study has several significant strengths. Firstly, most SC service referral studies were conducted in the health care settings [10, 28–30]; research conducted in the community settings is scarce [11]. The study fills this gap by providing an active referral intervention for community smokers who are not usually self-initiated to seek SC assistance. Secondly, follow-up assessments will be carried out at 1, 2, 3 and 6 months which allows us to keep longitudinal tracking on the effects of the active referral interventions on abstinence and changes in smoking-related psychosocial factors. Thirdly, the intervention approaches in this study (e.g., on-site active referral, text messaging, AWARD advice, referral card, self-help booklet) are brief and flexible. They can reach large numbers of community smokers at relatively low cost [11]. Therefore, the findings obtained will have significant implications for SC practice. Finally, the study will also have important implications for current SC policy, given the low utilization of SC services and a large number of cigarette smokers. If the intervention is effective in helping smokers to quit, our findings will address the active role of community health workers and SC service providers in promoting SC in the community.

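### The head-to-head question of high- versus low-intensity referral is stated as the objective but has no specified test; the main analysis and the sample size address intervention versus control

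*Protocol article*

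**What the plan says.** **Where the question is HAR versus Text.** The Abstract's background states: "The objective of this study is to compare 2 different intensities of SC active referral for smokers in the community of Hong Kong". The Discussion claims that "this is the first RCT conducted to evaluate whether high-intensity active referral to SC services is more effective than low intensity of SC referral", and then describes the study as going further by "comparing the efficacy of the 2 different intensities of SC active referral".

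**Where the aim is broader.** The Background says "This study aims to evaluate the effectiveness of 2 different intensities of active referral interventions", lists the two interventions and then describes the control group. The Abstract's closing discussion likewise expects evidence on the effectiveness of each. Both can be read as each intervention against control.

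**What is to be analysed.** Under Data analysis: "The main analysis will be a comparison between both intervention groups and the control group", for abstinence at 3 and 6 months, "using chi-square tests and odds ratios with 95% confidence intervals". Also, "Generalized Estimating Equation (GEE) models will be applied to test the intervention effect", without saying which groups that effect contrasts.

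**What the trial is sized for.** Sample size and power analysis uses 3-month abstinence of 18.7% under moderate-intensity active referral and 14% under control, taken from the 2015 contest. It arrives at 971 per arm and then caps recruitment at 1200, or 400 per group. No HAR-Text difference or precision is given.

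**One other mention.** The Discussion speaks of setting HAR, moderate-level referral and text referral side by side in a combined model over two years. The Data analysis section does not describe that model.

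**The concern.** The article does state its main contrast, and that contrast is not the one its abstract objective and novelty claim call for. This is a disagreement between stated rules, not a detail left to an analysis plan. A plan that followed the Data analysis section would keep the mismatch, and one that made HAR versus Text the main comparison would contradict that section.

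With no named contrast, the document does not say how intensity will be judged. The easy substitute is to note that one arm differs significantly from control and the other does not. That does not test a difference between the arms, since both are measured against the same control with limited power. The answer has practical weight, because the protocol describes Text as much the cheaper and briefer method, so whether HAR adds anything bears on which service is worth funding.

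**Working it through.** **1. The planned sample size is for intervention versus control.** Inputs: p1 = 0.14, p2 = 0.187, 80% power, 5% significance (two-sided assumed; the protocol does not say). With p̄ = 0.1635 and pooled variance,

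n = [1.96·√(2·p̄·(1−p̄)) + 0.8416·√(p1(1−p1) + p2(1−p2))]² / (p2−p1)²
= [1.96·√0.27354 + 0.8416·√0.27243]² / 0.047²
= (1.0251 + 0.4393)² / 0.002209 ≈ 971.

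This matches the stated 971 exactly. The one-sided version gives 765.

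**2. Precision of a direct HAR-Text contrast at 400 per arm.** The protocol gives no rate for either arm, so the rates below are assumptions built from its 14%, 18.7%, 1.33 and 1.54. The last two are used as odds ratios, by p' = p·OR/(1 − p + p·OR).

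- Power = Φ[(Δ − 1.96·SE0)/SE], with SE0 = √(2p̄(1−p̄)/400) and SE = √([pT(1−pT) + pH(1−pH)]/400).
- Half-width of the 95% confidence interval = 1.96·SE.

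| Text | HAR | Power | Half-width (points) | n per arm for 80% power |
|---|---|---|---|---|
| 14% | 18.7% | 43.5% | 5.1 | 971 |
| 18.7% | 23.4% (OR 1.33) | 37.4% | 5.6 | 1168 |
| 16.35% (midpoint of 14% and 18.7%) | 18.7% | 13.9% | 5.3 | 4108 |
| 17.8% (OR 1.33 on 14%) | 20.0% (OR 1.54 on 14%) | 12.5% | 5.4 | 4769 |

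Third row in full: SE = √((0.1635·0.8365 + 0.187·0.813)/400) = 0.0269 and SE0 = 0.0269. Power is Φ[(0.0235 − 0.0527)/0.0269] = Φ(−1.09) ≈ 0.14, and the half-width is 1.96 × 0.0269 = 0.053.

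Larger differences would do better. The smallest difference with 80% power at 400 per arm is 7.6 points from a Text rate of 14%, or 8.3 points from 18.7%.

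**3. Clustering.** Mean cluster size is 1200/68 = 17.6 and the design effect is 1 + 16.6·ICC. No ICC is given. For an assumed 0.01 to 0.05 the design effect is 1.17 to 1.83. The 43.5% then falls to between 38.3% and 26.3%, and the 12.5% to between 11.3% and 8.7%.

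**4. What happens if significance against control is compared.** Assume no clustering, 400 per arm and pooled z-tests.

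- *HAR and Text truly equal at 18.7%, control 14%:* each arm is significant with probability 0.435 and both with probability 0.272, the two tests being correlated through the shared control. Exactly one is significant with probability 2 × (0.435 − 0.272) ≈ 0.33.
- *HAR 18.7%, Text 16.35%, control 14%:* 0.435 and 0.152 individually, both 0.114. Exactly one: 0.435 + 0.152 − 2 × 0.114 ≈ 0.36.

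**5. Could the stated main analysis be a HAR-Text test under another reading?** The sentence does not say whether the two intervention arms are compared with control separately, pooled, or in one three-group test. The first two leave HAR versus Text out. A three-group test would respond to any difference among the groups and would not isolate that one.

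**The case against.** The strongest reply has four parts.

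- **The aim is also worded broadly.** The Background and the Abstract's closing discussion speak of the effectiveness of each intervention, and the main analysis and sizing serve that aim. This stands. The defect is that the aims disagree, and the gap is confined to the head-to-head question.
- **The GEE could supply the contrast.** A three-level group factor yields a HAR-Text estimate directly, and full lists of contrasts often sit in documents not shown here. It could, but the article defines no contrast for it while it does define the main one.
- **A combined model is announced.** The Discussion's two-year model would place HAR beside Text, so it would be wrong to say that the comparison is never contemplated. However, that model is absent from the Data analysis section and brings in a moderate-referral arm that this trial does not randomise. It does not replace the randomised contrast.
- **Nobody proposes to compare p-values.** A reader might infer that the authors will judge intensity by which arm beats control. No sentence says so. The document leaves the method open, and the one-in-three figure shows what that shortcut would cost if it were taken.

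It also stands that the added contrast would be weak at this sample size, and that nothing here makes the intervention-versus-control results invalid or biased.

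**Conclusion.** The point holds as an inconsistency. The abstract objective and the Discussion's claim ask whether HAR is better than Text, while the specified main comparison and the sample size concern intervention versus control, and no HAR-Text test is specified. A reader might conclude that the trial cannot test its objective at all. That goes too far, because the broader aim is tested and the GEE could produce the missing estimate.

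A direct contrast at 400 per arm would have about 12% to 44% power under the assumed rates, less with clustering, and a half-width a little over 5 points. Inferring intensity from discordant significance would mislead in about one trial in three if the arms were equal at the assumed 18.7% with control at 14%. A reader might also infer that discordance is likely by chance alone. The figures do not support that: it is a minority outcome in both scenarios, and in the 36% case HAR truly exceeds Text, so chance is not the only source.

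**What to change.** Settle one of two routes before unblinding.

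1. **Keep the head-to-head objective.** Name HAR versus Text as a pre-specified contrast from the same cluster-adjusted model, reported as an odds ratio and a risk difference with 95% confidence intervals. Give its place in the testing order. State its expected precision at 400 per arm, with the assumed rates and ICC. Add that no conclusion about intensity will be drawn from differing significance against control. Say whether the two-year combined model is supplementary.
2. **Keep intervention versus control as the question.** Reword the abstract objective and the Discussion's novelty claim to the effectiveness of each intervention against control, in line with the Background.

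The first route costs one extra contrast, which must be fitted into the testing order and will be imprecise. The second costs a few sentences. Neither needs more participants or data.

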**Methods/design:**

This is a single-blind, parallel 3-armed cluster randomized controlled trial (cRCT) consisting of high-intensity SC active referral (HAR Group), low-intensity SC referral by text messaging on promoting SC services use (Text Group) and a control group receives general very brief advice. Biochemically validated daily smokers will be proactively recruited in the community from 68 clusters (recruitment sessions). The primary outcome is self-reported 7-days point prevalence abstinence (PPA) at the 3- and 6- month follow-ups. Secondary outcomes are SC service use, smoking reduction rate (SRR, daily cigarette consumption reduced by ≥50%; excluding quitters) and biochemically validated quit rate (exhaled CO < 4 ppm and salivary cotinine < 10 ng/ml). Outcome assessors and data analysts will be blinded to group allocation. Intention-to-treat principle and Generalized Estimating Equation (GEE) regressions will be used for data analysis.

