### Recruitment

A total of 68 recruitment activities will be organized in all 18 Hong Kong districts aiming to recruit 1200 participants over 3 months. University students majoring in nursing, public health and related fields and volunteers of non-governmental organizations (NGOs) will be trained as SC ambassadors in a two-day workshop (8 h each) for onsite recruitment. To reach as many as eligible smokers, booths containing SC and recruitment information will be set up in shopping malls and public areas. Using persuasive techniques such as the ‘foot-in-the-door’ method [23], SC ambassadors will ask smokers simple questions (e.g., daily cigarette consumption, history of smoking, general health status) to arouse their interest in participating in the Contest. Informed consent for voluntary participation will be obtained from the eligible participants before administering the baseline questionnaire.

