### Randomization and blinding

cRCT design will be used in which all participants will be randomly assigned to 1 of the 3 groups based on the recruitment session. The randomization of group assignment will be generated before recruitment. One investigator who does not participate in recruitment will randomly generate blocks, with each block size equal to 3, 6 or 9, containing a random permutation of the 3 RCT groups. The numbers for the permutation in the blocks will be generated from the website http://www.random.org (a website for generating random integers), and then merge with the list of all recruitment days. As the intervention cannot be completely blinded in this study, the RCT is single-blinded that all outcome assessors and data analysts will be blinded to group allocation.

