#### Outcome assessments

The primary outcome is self-reported 7-day PPA at 3 and 6 months.

Secondary outcomes include:SC services use: calling a hotline of the SC services, booking an appointment, SC clinic attendance, counselling session attendance, and other indicators to be further specified after liaison with the existing SC services (e.g. services providers’ records on services utilization). The number of referrals will be calculated for the baseline and 1-, 2-, 3- and 6-month follow-ups.Biochemically-verified past 7-day PPA using exhaled-air CO levels < 4 ppm and saliva cotinine concentration < 10 ng/ml [26, 27].Smoking reduction is defined as daily cigarette consumption reduction by > 50% compared with baseline.

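### The test named as the main analysis, an ordinary chi-square with odds-ratio intervals, ignores the randomisation of 68 recruitment sessions; the planned GEE, clustered on session, should take its place

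*Protocol article*

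**What the plan says.** The abstract and the Overview of design both describe a three-arm cluster randomised trial. Under Randomization and blinding the article says "cRCT design will be used in which all participants will be randomly assigned to 1 of the 3 groups based on the recruitment session". Under Recruitment it says "A total of 68 recruitment activities will be organized in all 18 Hong Kong districts aiming to recruit 1200 participants over 3 months".

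Under Outcome assessments, "The primary outcome is self-reported 7-day PPA at 3 and 6 months". The Data analysis section names as the main analysis a comparison of each intervention group with control on the abstinence proportions at those two times, "using chi-square tests and odds ratios with 95% confidence intervals". No allowance for session is attached to this test.

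The next sentence adds a second method: "Generalized Estimating Equation (GEE) models will be applied to test the intervention effect, to identify the baseline predictors of successful quitting", with change over time as a third use. The abstract mentions only the second method: "Intention-to-treat principle and Generalized Estimating Equation (GEE) regressions will be used for data analysis". Neither place says which unit forms the GEE cluster.

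**The concern.** Smokers enrolled at one session share a venue, a day and a recruiting team, so their outcomes may be correlated. An ordinary chi-square, and the odds-ratio interval that goes with it, take their standard error from independent individuals. When whole sessions are allocated and outcomes within a session are positively correlated, that standard error is too small. The headline comparison of either intervention with control would then reject a true null hypothesis more often than the 5% stated, and the reported interval would be too narrow.

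The plan already contains a method that could deal with this, but the label of main analysis sits on the one that cannot. Two tests of the same effect, of which only the invalid one is designated as main, also leave room for choosing between them if they disagree.

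**Working it through.** **Inputs from the article.** 68 sessions and 1200 participants (Recruitment); 400 per arm, rates of 14% and 18.7%, 5% significance, 80% power and 971 per arm (Sample size and power analysis). Mean session size m = 1200/68 = 17.65; sessions per arm = 68/3 = 22.7, that is 22 or 23.

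**Input assumed.** The ICC. The article gives none, so a range from 0 to 0.05 is used.

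**Step 1: is clustering in the plan's own sample size?** The usual two-proportion formula (two-sided, pooled variance under the null, no continuity correction) is

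n = [1.96·√(2·p̄(1−p̄)) + 0.8416·√(p₁(1−p₁) + p₂(1−p₂))]² / (p₂−p₁)²

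With p₁ = 0.14, p₂ = 0.187 and p̄ = 0.1635:

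n = [1.96 × 0.5230 + 0.8416 × 0.5220]² / 0.047² = 2.144 / 0.002209 = 970.7, rounded up to **971**.

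The stated figure reproduces exactly as an individually randomised comparison. It contains no design effect, which agrees with reading the main test as an individual-level one.

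**Step 2: effect of ignoring sessions.**

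- Design effect: DE = 1 + (m − 1) × ICC.
- Ratio of correct to naive interval width (log odds ratio scale): √DE.
- True two-sided type I error of a nominal 5% test: 2 × (1 − Φ(1.96/√DE)).

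Example at ICC 0.02: DE = 1 + 16.65 × 0.02 = 1.333; √DE = 1.155; 1.96/1.155 = 1.697; error = 2 × (1 − Φ(1.697)) = 9.0%.

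The formula was checked by a beta-binomial simulation of the null: 23 v 23 sessions of 17, quit rate 14%, 40,000 runs per ICC.

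| Assumed ICC | DE | Correct interval wider by | Type I error, formula | Type I error, simulated chi-square | Simulated session-level t-test |
|---|---|---|---|---|---|
| 0 | 1.00 | 0% | 5.0% | 5.0% | 4.9% |
| 0.001 | 1.017 | 1% | 5.2% | not run | not run |
| 0.005 | 1.083 | 4% | 6.0% | 5.6% | 4.9% |
| 0.01 | 1.166 | 8% | 7.0% | 7.0% | 5.2% |
| 0.02 | 1.333 | 15% | 9.0% | 8.9% | 4.9% |
| 0.05 | 1.832 | 35% | 14.8% | 14.7% | 5.0% |

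The session-level t-test on the same simulated data stays near 5%, so the excess comes from ignoring the session.

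**Step 3: unequal sessions.** With a coefficient of variation (CV) of session size, DE = 1 + ((1 + CV²)·m − 1) × ICC. For an assumed CV of 0.5 and ICC 0.05, DE = 1 + (1.25 × 17.65 − 1) × 0.05 = 2.053 and the error is 17.1%. At ICC 0.02, DE is 1.421 and the error 10.0%.

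**Step 4: cost in power of a valid test.** The effective size per arm is 400/DE. For 14% v 18.7%, two-sided, power at 400 independent participants per arm is 43.5%. At ICC 0.01, 0.02 and 0.05 the effective sizes are 343, 300 and 218, and power is 38.3%, 34.3% and 26.3%.

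**The case against.** The strongest reply is that the plan does contain a suitable method. The first use given for GEE in the Data analysis section is testing the intervention effect, and the abstract, which calls the trial cluster randomised, names GEE regressions and no chi-square. A reader could fairly say that the article is unclear about which analysis governs, and that the cluster variable and working correlation are details commonly left to a fuller document.

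Much of that stands. A reader might infer that the trial has no means of handling clustering, or that GEE is meant only for repeated measures within a person because it is also planned "to identify the baseline predictors of successful quitting and to assess the changes in smoking-related factors over time". The documents support neither inference. The longitudinal use is one of three and does not show how the intervention effect itself will be modelled, and silence about the cluster variable is not in itself an error in an article. What the reply does not remove is the explicit designation. The article does not leave the main test to another document: it names one, and that test does not match the unit of randomisation.

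A second reply is that no ICC is given, so inflation is not certain. That is right. At ICC 0.001 the error is 5.2%, which is harmless, and the point has to be stated conditionally.

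Two further inferences should not be drawn. An unadjusted comparison is not an error in a randomised trial, so the lack of covariates in the chi-square is no fault. Nor does the article establish that the recruiting ambassadors deliver every arm: it describes them booking services on site for the HAR group, but does not say who gives the brief advice in the other arms. Differential enrolment would also be a question of bias, which a clustered standard error does not address.

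**Conclusion.** The point holds: the test designated as the main analysis ignores the allocation of whole sessions, and this is a stated method rather than a missing detail. Its consequence is conditional on a positive ICC. For ICCs from 0.005 to 0.05 the true error rate is roughly 6% to 15% with near-equal sessions, and somewhat higher if session sizes vary. These figures rest on the assumed ICC range, a mean of 17.6 smokers per session, 22 to 23 sessions per arm and, in the simulation, a 14% quit rate. It would go too far to say that the p-values will certainly be too small, or that clustering-capable modelling is absent from the plan.

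**What to change.** Reword the Data analysis section so that the logistic GEE already planned is the main analysis of abstinence at 3 and at 6 months. Name the recruitment session as the cluster and use robust standard errors with a small-sample correction, since each comparison with control involves only about 45 sessions (2 × 68/3 = 45.3). If both times are put in one model, keep the session as the cluster, because each participant's repeated measures are nested within it. Report the odds ratios and 95% confidence intervals from that model together with the observed ICC, and keep the chi-square as descriptive only. Covariate adjustment is optional. If used, it should be specified in advance, because it changes the odds ratio being estimated.

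The cost is one paragraph of wording and no new data, since the group assignments are already merged with the list of recruitment days; each participant's session only has to be carried into the data set. The price in results is wider intervals, by up to about a third at ICC 0.05 with near-equal sessions, and lower power than the individual-level calculation implies. The sample size section should acknowledge this with an assumed ICC.
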